#### The ELICIT study (Tanzania)

2.1.2

The Early Life Interventions for Childhood Growth and Development in Tanzania (ELICIT) study is a double-blind, placebo-controlled randomized trial with a 2 × 2 factorial design conducted in Haydom, a rural area in Tanzania (NCT03268902). This study’s primary objective was to determine if infant antimicrobials and/or maternal and infant nicotinamide improve infant growth by the age of 18 months (49). At enrollment, dyads were randomly assigned to either the infant antimicrobial intervention and placebo, placebo and maternal and infant nicotinamide intervention, both interventions, or two placebos (no interventions). The antimicrobial intervention was given to the infant as a dose of azithromycin at 6, 9, 12, and 15 months, and a 3 day course of nitazoxanide at 12 and 15 months. The nicotinamide intervention was a daily dose of 250 mg nicotinamide to breastfeeding mothers from 0 to 6 months, followed by 100 mg daily to the child from 6 to 18 months. The study recruited 1,188 mother/infant dyads, enrolled before age 2 weeks between 5 September 2017 and 31 August 2018 and followed children through age 18 months. The primary outcomes of this trial have been published elsewhere (57). For a subset of 200 dyads, IMiC will access HM samples collected at 1 and 5 months and data collected through 18 months.

HM was collected as follows: milk samples were collected mid-feed. Mothers cleansed the breast around the areola with soap and water, rinsing with deionized water. Approximately 8 mL of milk was hand-expressed into a wide-mouthed sterile container. The container was then placed on ice before being transported to the laboratory, where milk was aliquoted, shielded from light, and kept at −80°C until transportation to a central biorepository for IMiC.

#### The VITAL Lactating Women study (Pakistan)

2.1.3

The VITAL-Lactating Women (VITAL-LW) trial, also known as the MUMTA trial (MUMTA is an Urdu acronym for “nutritional support for lactating women with or without azithromycin”), is an assessor-blinded 3-armed randomized control trial conducted in Karachi, a peri-urban area in Pakistan (50) (NCT03564652). The primary objective was to identify the impact of a fortified, balanced energy protein (BEP) supplements consumed by lactating women on child growth outcomes, and to determine whether prophylactic antimicrobials provide added benefits to BEP supplementation. Lactating mothers were randomly assigned to 3 groups at enrollment: BEP intervention only, BEP with a single dose of prophylactic azithromycin to the infant at 42 days of age, or control (no interventions) (50). The BEP supplement was 2 sachets given daily from birth to 6 months postpartum. VITAL-LW recruited 957 breastfeeding mother-infant dyads between 2018 and 2020. Primary outcomes are published separately (58). For a subset of 150 dyads, IMiC will access HM samples collected at 42 and 56 days postpartum and data collected until 12 months.

HM was collected as follows: Immediately prior to breastfeeding, the breast around the areola was washed with warm water and soap and dried with a single-use cloth. At least 10 mL of milk was hand expressed directly into a sterile collection container and kept at 2°C–8°C in a box with ice packs during transport to a laboratory for aliquoting. Milk samples were mixed well prior to aliquoting into 4 sterile 1.5 mL cryovials and stored at −80°C until transportation to a central biorepository for IMiC.

#### The MISAME-3 study (Burkina Faso)

2.1.4

The MIcronutriments pour la SAnté de la Mère et de l’Enfant 3 (MISAME-3) is a 4-arm randomized controlled trial conducted across 6 health centers in the Houndé region in rural Burkina Faso (NCT03533712). This study’s primary objective is to assess the effect of a balanced energy protein (BEP) supplement during pregnancy and/or lactation on birth outcomes and infant growth (51). At enrollment, women were randomly assigned to either prenatal intervention, postnatal intervention, both prenatal and postnatal intervention, or no intervention (control). The intervention was a BEP supplement taken daily by the mother, while both the intervention and control groups received iron/folic acid (IFA) tablets until 6 weeks postpartum. Prenatal BEP supplementation started at enrollment (<21 weeks gestation), and postnatal BEP supplementation started at delivery and continued for 6 months. The study recruited 1,708 pregnant women who gave birth to 1,628 singleton infants between 2020 and 2021. Primary outcomes of this trial have been published elsewhere (59, 60). For a subset of 290 dyads, IMiC will access HM samples collected at 14–21 days, 1–2 months and 3–4 months, and data collected during pregnancy and the first year postpartum.

HM was collected as previously described (61). Briefly, an electric breast pump (Medela, Baar, Switzerland) was employed for full expression from the breast that was not most recently used to feed the infant. The sample was then gently inverted to homogenize fore- and hindmilk. A total volume of 7.2 mL of milk was extracted from this full expression volume, and then aliquoted into 4 × 2 mL sterile cryotubes. Samples were stored in insulated bags with ice packs at home before being collected on the same day by study staff. Samples were then transferred to liquid nitrogen storage vessels and stored at −80°C in the health center before being transported to a central biorepository for IMiC.

Notably, the BEP supplement used in VITAL-LW was primarily derived from chickpeas and lentils whereas in MISAME-3 it was primarily derived from peanut paste. The exact formulations for each study differed, and are described elsewhere (58, 60, 62).

### Eligibility criteria and selection of the IMiC subset

2.2

All study participants provided voluntary informed consent. Each study determined their eligibility criteria (summarized in Table 2) based on their primary study objectives. Further details on the consent process and eligibility criteria can be found in the protocols for each study (49–51, 55). Additional criteria used to select the “IMiC subset” from each study are described below. A notable but inevitable bias introduced through this selection process is that dyads who had stopped breastfeeding before the time of HM sample collection (or who never breastfed at all) could not be included.

#### CHILD

2.2.1

A total of 2,800 CHILD mothers provided a HM sample, of which 400 were selected for IMiC. Selection was based on prioritizing dyads who had not already had their HM samples analyzed, and achieving representation across different infant growth trajectory categories, assigned using latent class trajectory analysis of WHO weight-for-age z-scores from birth until 5 years. Specifically, we followed the following steps: (1) infants without weight and/or length data at birth, 3 months or 12 months were excluded, (2) infants in the category with the most rapid growth were excluded due to low sample size, (3) all infants in the category with the second most rapid growth (*n* = 55) were included regardless of whether they had already had HM samples analyzed previously (*n* = 39) or not (*n* = 13) since this is an important yet relatively small group, (4) for selection of the remaining 348 milk samples, in addition to above mentioned exclusion criteria, HM samples that were already analyzed as part of previous CHILD studies (*n* = 1,200) were excluded and then (5) all remaining infants in the persistently overweight category (*n* = 63) were included and (6) an equal proportion of infants were selected from the remaining 4 categories (Stable −1 z-score, stable 0 z-score, low birth weight - stable, and stable 1 z-score; *n*~70 per group). Selection for these remaining 4 categories followed additional criteria: (1) priority was given to dyads that had infant gut microbiome data available or those expected to have gut microbiome data available in the future, (2) an approximately equal representation across CHILD study sites within each of the 4 categories, and (3) among Toronto infants, priority was given to infants with pulmonary function data (a clinical assessment only performed at the Toronto site).

#### ELICIT

2.2.2

1,177 out of 1,188 women enrolled in the ELICIT study provided HM samples, and of these, 200 women were selected for inclusion in IMiC. After excluding women who did not provide HM samples at both study time points, we randomly selected an approximately equal number from each study group (*n* = 50 women × 4 intervention groups) from a larger subset of 400 mothers selected based on data completeness (infant blood samples collected and anthropometry measurements at all time points) and for an approximately even distribution over the recruitment year.

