#### VITAL-LW

2.2.3

Of the 957 women enrolled in the VITAL-LW trial, 150 (*n* = 50 × 3 intervention groups) were selected to provide HM samples for IMiC. Selection criteria for these 150 participants included agreement to provide all maternal and infant samples and availability to follow-up until at least the 6 month visit.

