#### Intervention effects analysis

2.9.3

We will also estimate the effects of randomized interventions on human milk components in the three intervention studies. Two different definitions of ‘milk composition’ will be used (1) individual milk components, adjusted for multiple testing and (2) predictive summary measures calculated from milk biomarkers of infant growth using targeted learning and other dimension reduction techniques (96). We will estimate both unadjusted and covariate-adjusted intervention effects on each HM outcome, adjusting for baseline prognostic factors using cross-validated targeted maximum likelihood estimation (97). In addition to analyzing HM components at each time point, we will also examine changes in HM components between timepoints. We will correct for multiple comparisons by using the Benjamini-Hochberg procedure, and group corrections by time-point and outcome group. Primary outcomes are macro- and micro-nutrients, secondary outcomes are HMOs and targeted proteins and bioactives, tertiary outcomes are targeted metabolomics, and exploratory outcomes and untargeted metabolomics, untargeted proteomics, and the microbiome.

As a secondary analysis, we plan to assess the potential mediating effects of HM components on the relationship between maternal nutritional supplementation or other maternal factors, and infant growth outcomes (Supplementary material).

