### Challenges

3.2

General challenges for the IMiC consortium include: (1) the administrative burden and complexity of financial and legal agreements for subgrants, data sharing and/or material transfer across 13 institutions; (2) the logistical burden and complexity of shipping frozen human milk across countries and continents; (3) communication challenges related to geographic and cultural diversity; (4) data harmonization challenges stemming from the different study designs and data collection time points; and (5) ensuring equitable representation, participation, collaboration and attribution for all members, including those from low-middle-resource and low-middle-income country (LMIC) settings. The latter has been the primary focus of the IMiC LMIC working group, whose work will be described elsewhere.

Selection bias and generalizability are challenges of particular note in our study, where participants were selected partially based on data availability across independent studies across diverse settings. For instance, only participants able to provide milk samples and attend follow-up visits for infant anthropometric measurements could be included, and unmeasured maternal or socioeconomic factors could differ between those able to participate and all eligible participants, leading to potential biases in the associations identified (98). We will implement strategies to mitigate selection bias during the data analysis phase (e.g., through careful consideration of handling missing data) and will consider its unintended effects during the knowledge translation phase, such as lack of transferability of some conclusions across geographic settings. We will also be sure to use the most relevant reference standards for the diverse populations we are studying (e.g., using mid upper arm circumference rather than BMI to identify maternal undernutrition, and using international infant growth standards that have been validated across different ethnic groups).

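### ELICIT's randomised milk comparison is restricted to dyads selected on completeness after randomisation, and no method the article describes deals with the dyads left out

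*Protocol article*

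**What the plan says.** Section 2.1.2 places randomisation first: "At enrollment, dyads were randomly assigned". Table 2 puts enrolment at 14 days of infant age or less. Children were then followed to 18 months.

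Section 2.2.2 describes how the ELICIT subset was formed. It starts from near-complete milk donation: "1,177 out of 1,188 women enrolled in the ELICIT study provided HM samples". Two filters follow. The first is "After excluding women who did not provide HM samples at both study time points". The second is that the final 200 were drawn at random, about 50 per group, "from a larger subset of 400 mothers" who had been "selected based on data completeness (infant blood samples collected and anthropometry measurements at all time points") and for an even spread over the recruitment year.

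Section 2.9.3 then states: "We will also estimate the effects of randomized interventions on human milk components in the three intervention studies". It gives unadjusted estimates and estimates adjusted for baseline factors by cross-validated TMLE.

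Sections 2.2 and 3.2 acknowledge selection bias. Section 3.2 promises strategies to reduce it at the analysis stage, with one example: "e.g., through careful consideration of handling missing data".

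**The concern.** Both filters depend on what happened after randomisation. A dyad without the 5-month sample is absent from the 1-month comparison too. If all time points means the whole of ELICIT follow-up, inclusion in a 1-month milk comparison depends on visits up to 17 months later. Drawing equal numbers per group after filtering also hides any difference between arms in how many dyads were complete.

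Randomisation protects the comparison of everyone randomised. It does not automatically protect a comparison of those who later proved complete. An effect reported simply as that of the randomised intervention would in fact describe a selected group, and it could be biased if the groups were selected differently. The article names no step that would reveal or correct this.

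**Working it through.** **1. The plan's own figures.** 50 women × 4 groups = 200 dyads, and 200 × 2 time points = 400 samples. Both agree with Table 2.

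**2. How much of the trial is used** (section 2.2.2).
- 1,177/1,188 = 99.1% gave milk.
- The pool is 400/1,188 = 33.7% of those enrolled.
- The final set is 200/1,188 = 16.8%, which leaves 1,188 − 200 = 988 randomised dyads outside the comparison.

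These shares do not measure loss through incompleteness. The step from 400 to 200 is a random draw within group, and the 400 were also chosen for spread over the year. The number excluded for incompleteness, overall or by arm, is not given.

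**3. Order of events** (sections 2.1.2 and 2.2.2). Randomisation comes by 14 days, milk at 1 and 5 months, and the maternal nicotinamide period is 0 to 6 months. The infant antimicrobials and the child nicotinamide start at 6 months, and follow-up ends at 18 months. On the natural reading of all time points, the completeness window therefore includes randomised treatment given after both milk samples.

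**4. Reach of the missing-data methods.** Section 2.7.2.3 filters sparse features, imputes values beyond detection limits, and fills the remaining gaps by random forest. Each step acts on analytes in included samples. None restores a dyad that was never included. The baseline adjustment in section 2.9.3 can absorb part of an imbalance in measured factors, but no selection model is mentioned.

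**5. Precision.** On the nicotinamide margin of the factorial design (100 v 100), in SD units:
- SE = √(2/100) = 0.141.
- Difference detectable with 80% power = (1.960 + 0.842) × 0.141 = 0.40.

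**6. A simple bound on assumed inputs.** Bias ≈ (difference in incompleteness between arms) × (milk difference between complete and incomplete dyads). With 5 to 10 points and 0.5 SD, bias = 0.05 × 0.5 = 0.025 to 0.10 × 0.5 = 0.05 SD. That is 0.025/0.141 = 0.18 to 0.05/0.141 = 0.35 standard errors.

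**7. A selection model on assumed inputs, true effect zero.** Frailty U is standard normal and the milk value is rU + √(1 − r²)e, with e standard normal and independent of U. The probability of being complete is logistic in U, with slope −1 in both arms, or −1 in one arm and 0 in the other. Each cell gives the bias in SD and the two-sided rejection rate at 100 v 100.

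| Complete, arm 1 / arm 2 | Slope | r = 0.2 | r = 0.5 |
|---|---|---|---|
| 90% / 90% | both arms | 0.000; 5.0% | 0.000; 5.0% |
| 85% / 90% | both arms | 0.008; 5.0% | 0.021; 5.2% |
| 80% / 90% | both arms | 0.016; 5.2% | 0.041; 6.0% |
| 70% / 90% | both arms | 0.032; 5.6% | 0.081; 8.8% |
| 85% / 85% | arm 1 only | 0.027; 5.4% | 0.066; 7.6% |
| 70% / 90% | arm 1 only | 0.051; 6.5% | 0.126; 14.5% |

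**8. Does weighting help?** In one arm with 70% complete and r = 0.5, the mean among selected dyads is −0.125. Weighted by the inverse of the selection probability it is 0.001, and the full-sample mean is 0.001. This holds because U is treated as measured on everyone.

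**The case against.** The authors disclose the selection in sections 2.2 and 3.2, and the choice of mitigation may lie in supplementary material that is not shown. The disclosure is real, but section 3.2 speaks of bias in associations and does not mention the randomised contrast. Section 2.2 calls unavoidable only the loss of dyads no longer breastfeeding at sampling. Requiring the 5-month sample for the 1-month comparison, and complete infant data, was a choice.

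Several stronger readings are tempting and are not supported:

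- *Missing-data handling cannot correct this.* Section 3.2 offers it only as an example. Treating unselected dyads as missing, through weights or a TMLE with a selection mechanism, is also missing-data handling and could work for measured factors. What fails is the set of methods the article describes.
- *The ELICIT contrast is biased.* ELICIT was double-blind and placebo-controlled, and completeness by arm is not reported. If selection works the same way in both arms, the bias in step 7 is zero.
- *Deaths and drop-outs were removed up to 18 months.* The article reports no such events for ELICIT and does not say when the last required time point fell. Both are inferences from the rule.
- *Data on unselected dyads are unavailable.* Section 2.8.1 says each study provides a subset of its dataset, which may mean a subset of variables.
- *VITAL-LW has the same fault.* Its criterion, "availability to follow-up until at least the 6 month visit", reads as a condition set before milk collection, not as selection of completers.
- *The milk–growth associations are biased as well.* Losing infants who falter could shift the growth distribution, but a shifted distribution does not show a biased association.

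**Conclusion.** The point holds in limited form. ELICIT's randomised milk comparison is conditioned on completeness after randomisation, and neither the missing-data methods nor the baseline adjustment described in the article addresses the excluded dyads.

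Whether this matters for the arm contrast depends on facts not given: whether completeness differed by arm, and whether its drivers relate to milk. If not, the estimate is sound for the selected group and only its generalisability suffers. On modest assumptions the bias is 0.025 to 0.05 SD, about a third of a standard error at most. It approaches 0.13 SD, with a false-positive rate near 14.5%, only when selection differs strongly between arms and milk is fairly closely tied to frailty. All of these sizes rest on assumed inputs and none is an estimate for ELICIT. The case for a change is that the matter can be checked with data the parent trial should already hold.

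**What to change.** Use existing ELICIT trial data on arm, enrolment covariates and follow-up status for all 1,188 randomised dyads.

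1. Report by arm how many dyads had both milk samples, how many had complete infant blood and anthropometry, and which time points the rule covered.
2. Compare selected with unselected dyads at baseline.
3. Beside the unweighted estimate, give a sensitivity estimate weighted by the inverse of the inclusion probability, or a TMLE that includes the selection mechanism. Model inclusion on arm and enrolment covariates, and allow for the spread over the recruitment year and the random draw.
4. Describe the unweighted ELICIT effect as applying to dyads with both milk samples and complete infant data.
5. In section 3.2, name this analysis in place of the general example.

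The cost is a transfer of existing data under the sharing agreements, one further analysis and somewhat wider intervals. The subset and the assays stay as they are. Weighting will not correct for unmeasured drivers, and it cannot supply milk values that do not exist, such as 5-month milk from a mother who had stopped breastfeeding.

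The weighting should not be extended to VITAL-LW or MISAME-3 by default. In MISAME-3 the biospecimen sub-study opened after trial recruitment had closed and took women by gestational age (section 2.2.4), so some randomised women may have had almost no chance of inclusion and weights to the full trial could be unstable.

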#### VITAL-LW

2.2.3

Of the 957 women enrolled in the VITAL-LW trial, 150 (*n* = 50 × 3 intervention groups) were selected to provide HM samples for IMiC. Selection criteria for these 150 participants included agreement to provide all maternal and infant samples and availability to follow-up until at least the 6 month visit.

#### MISAME-3

2.2.4

Of the 1,708 women enrolled in the MISAME-3 study, 290 provided milk samples and all were selected for inclusion in IMiC. This subset of mothers and their infants were part of the BioSpé sub-study of MISAME-3, contributing other biospecimen samples (i.e., plasma, blood, cord blood, feces and urine) at multiple time points (61). The BioSpé study was initiated following the completion of recruitment for the MISAME-III trial, when most participants were in their third trimester. To maximize the recruitment of participants in their second trimester, women were prioritized based on gestational age in descending order, ensuring an even distribution across all four study intervention groups. Ultimately, 309 women and their infants were enrolled into the BioSpé study, of which 290 provided milk samples.

### Study participants

2.3

Participant demographics and growth outcomes are summarized in Table 3, showing high inter-study heterogeneity for many characteristics. Compared to the three low-middle resource studies, mothers in the Canadian CHILD cohort tend to be older with more education and higher BMIs, and were more likely to be primiparous. For instance, CHILD mothers had a mean age of 33 (±4) years and nearly half (48%) were primiparous, whereas MISAME mothers were nearly a decade younger (mean age 24 ± 6 years), yet only 26% were primiparous. All CHILD households and nearly all VITAL households (95%) had “improved water sources,” compared to just 59% in MISAME and 66% in ELICIT. CHILD mothers had a mean BMI of 24.2 (±4.7) kg/m^2^ with many classified as overweight or obese (32%) and very few underweight (<5%). Compared to CHILD, mothers from the low-middle resource studies had relatively lower mean BMIs, ranging from 19.8 in VITAL to 22.5 in ELICIT, and relatively higher prevalence of underweight (7% in MISAME, 10% in ELICIT, and 20% in VITAL where low mid-upper arm circumference (MUAC) was an eligibility criterion). Only 7% of CHILD newborns were small for gestational age, compared to 25% in MISAME and 38% in VITAL (birth weight and gestational age were unavailable for ELICIT where enrollment occurred up to 14 days after birth). By 3 months, 13 to 15% of infants were stunted in the low-middle resource studies, compared to just 2% in CHILD. The mean duration of exclusive breastfeeding was longer in the low-middle resource studies (range 5–6 months) compared to CHILD (3.2 ± 2.4 months).

**Table 3 tab3:** Participant characteristics of mother-infant dyads included among 4 studies comprising the International Milk Composition (IMiC) Consortium.

Variable	CHILD	ELICIT	VITAL-LW	MISAME-3	Overall
Location	Canada	Tanzania	Pakistan	Burkina Faso	-
Birth years	2009–2012	2017–2018	2018–2019	2021	-
N dyads in IMiC	399	200	150	290	1,039
Mother at baseline^a^					
Age	32.5 (4.4)	29.4 (7.1)	24.2 (4.9)	24.2 (5.6)	28.4 (6.6)
Parity	1.8 (0.9)	4.4 (2.6)	2.7 (1.9)	2.9 (1.8)	2.7 (2.0)
Gravida	2.2 (1.3)	-	3.1 (2.2)	3.1 (1.9)	2.7 (1.7)
MUAC (cm)	-	-	21.5 (1.2)	26.1 (2.7)	24.6 (3.2)
HGB (g/dL)	-	-	-	11.7 (1.4)	11.7 (1.4)
Weight (kg)	65.7 (14.0)	55.9 (10.1)	46.1 (5.2)	58.1 (9.6)	58.1 (12.6)
Height (m)	1.65 (0.07)	1.58 (0.06)	1.52 (0.06)	1.62 (0.06)	1.59 (0.07)
BMI (kg/m2)	24.2 (4.7)	22.5 (3.7)	19.8 (1.7)	22.0 (3.1)	22.4 (4.0)
BMI category					
Underweight	18 (5%)	21 (10%)	30 (20%)	21 (7%)	84 (8%)
Normal	249 (64%)	134 (67%)	120 (80%)	229 (79%)	673 (65%)
Overweight	82 (21%)	35 (18%)	0 (0%)	36 (12%)	133 (13%)
Obese	42 (11%)	10 (5%)	0 (0%)	4 (1%)	43 (4%)
Birth					
Cesarean delivery	82 (21%)	0 (0%)	24 (16%)	6 (2%)	112 (11%)
Rainy season^b^	-	107 (54%)	45 (30%)	227 (78%)	379 (36%)
Home and socioeconomicstatus					
Improved water^c^	399 (100%)	131 (66%)	143 (95%)	172 (59%)	845 (81%)
Separate cooking space	-	124 (62%)	142 (95%)	0 (0%)	266 (26%)
Improved flooring	399 (100%)	-	146 (97%)	175 (60%)	720 (69%)
Mother’s education (yrs)	16.8 (2.9)	6.5 (2.7)	7.7 (3.1)	3.2 (3.9)	10.1 (6.8)
Infant at birth					
Sex (Female)	188 (47%)	101 (50%)	84 (56%)	148 (51%)	521 (50%)
Gestational age (wks)	39.6 (1.4)	-	38.9 (1.5)	39.8 (1.5)	39.6 (1.5)
Gestational age method					
Ultrasound	399 (100%)	-	86 (57%)	290 (100%)	775 (75%)
Last menstrual period	0 (0%)	-	64 (43%)	0 (0%)	64 (6%)
Birth weight (g)	3,412 (517)	3,190 (510)^d^	2,790 (410)	3,013 (449)	3,163 (537)
Birth length (cm)	51.5 (2.7)	49.1 (2.2)^d^	48.2 (1.9)	48.5 (2.1)	49.8 (2.7)
Preterm (<37 weeks)	17 (4%)	-	16 (11%)	11 (4%)	44 (4%)
Small for gestational age	28 (7%)	-	57 (38%)	73 (25%)	158 (15%)
Infant at 3 months					
Weight (kg)	6.2 (0.9)	5.7 (0.7)	5.2 (0.8)	6.0 (0.8)	5.9 (0.9)
Length (cm)	61.9 (3.0)	58.6 (2.1)	57.9 (2.3)	59.2 (2.8)	59.8 (3.0)
Head circumference (cm)	40.6 (1.6)	39.7 (1.4)	38.4 (1.3)	39.5 (1.5)	39.7 (1.6)
WAZ	−0.06 (1.13)	−0.56 (1.00)	−1.22 (1.21)	−0.21 (1.05)	−0.40 (1.16)
LAZ	0.41 (1.28)	−0.93 (1.02)	−1.10 (1.13)	−0.66 (1.25)	−0.44 (1.34)
WLZ	−0.38 (1.20)	0.30 (1.33)	−0.38 (1.18)	0.51 (1.17)	0.06 (1.28)
HCAZ	0.28 (1.27)	−0.23 (1.11)	−1.14 (1.03)	−0.42 (1.09)	−0.24 (1.23)
MUACZ	-	-	12.28 (1.21)	13.13 (1.09)	12.88 (1.19)
Stunting^e^	8 (2%)	29 (14%)	23 (15%)	37 (13%)	97 (9%)
Wasting^f^	27 (7%)	7 (4%)	10 (7%)	5 (2%)	49 (5%)
Breastfeeding (BF)					
EBF duration (months)	3.2 (2.4)	5.1 (0.9)	5.9 (0.6)	5.8 (1.0)	4.7 (2.0)
BF status at 6 months					
Exclusive BF	79 (20%)	89 (44%)	141 (94%)	204 (70%)	513 (49%)
Partial BF	303 (76%)	111 (56%)	9 (6%)	85 (29%)	508 (49%)
No BF	13 (3%)	0 (0%)	0 (0%)	0 (0%)	13 (1%)

Values are *n* (%) or mean (standard deviation). BMI, Body mass index; HGB, blood hemoglobin; MUAC, Mid-upper arm circumference; HCAZ, head circumference for age z-scores; WAZ, weight for age z-score; LAZ, length for age z-score; WLZ, weight for length z-score; EBF, Exclusive breastfeeding; BF, Breastfeeding. ^a^Maternal baseline characteristics: parity at delivery, first measurement used for other characteristics (within the first 15 days after birth for ELICIT and VITAL-L and prenatal measures for MISAME-3 and CHILD). ^b^Rainy season refers to January until April for ELICIT and Late Summer/Monsoon for VITAL-L. ^c^Improved water definition adapted from WHO/UNICEF (73). ^d^Exact birth weight and length for ELICIT are unavailable, measurements were within the first 15 days after birth. ^e^Stunting = Infant LAZ < −2, ^f^Wasting = Infant WLZ < −2.

